## Abstract

**Background:**

People with depression/anxiety are twice as likely to smoke and are less responsive to standard tobacco treatments, leading to a reduced life expectancy of up to  13.6 years compared to people without depression/anxiety. However, this group of smokers is motivated to quit, and as a result of quitting smoking, their depression/anxiety is likely to improve. In England, people with depression/anxiety are referred to a primary care-based psychological therapies service known as ‘Improving Access to Psychological Therapies’ (IAPT), which could offer smoking cessation treatment as part of usual care but currently does not. In this study, we aim (1) to establish the feasibility and acceptability of delivering a smoking cessation treatment alongside IAPT usual care and (2) to establish the feasibility of a multi-centre randomised trial to compare the combined smoking cessation and IAPT treatment to usual IAPT treatment alone.

**Methods:**

A randomised and controlled, multi-centre trial to test the acceptability, feasibility and implementation of smoking cessation treatment as offered alongside usual IAPT care, compared to usual care alone, with nested qualitative methods. We will include adult daily smokers with depression/anxiety, who would like help to quit smoking and are about to start IAPT treatment. Follow-up will be conducted at 3-months after baseline. The main outcome will be retention in the smoking cessation treatment. Secondary outcomes are smoking-related (biochemically-verified 7-day point prevalence smoking cessation, number of cigarettes smoked per day, Heaviness of Smoking Index), mental health-related (PHQ-9), service-related (number of ‘Did Not Attends’, number of planned and completed IAPT sessions), acceptability and feasibility (participant and clinician acceptability and satisfaction of intervention as assessed by questionnaires and qualitative interviews, interviews will also explore acceptability and feasibility of data collection procedures and impact of smoking cessation treatment on usual care and mental health recovery) and implementation-related (intervention delivery checklist, qualitative analysis of intervention delivery).

**Discussion:**

If the intervention is shown to be acceptable, feasible and suitably implemented, we can conduct a randomised controlled trial. In a future trial, we would examine whether adding smoking cessation treatment increases smoking abstinence and improves depression and anxiety more than usual care, which would lead to long-term health improvement.

**Trial registration:**

ISRCTN99531779

**Electronic supplementary material:**

The online version of this article (10.1186/s40814-018-0385-2) contains supplementary material, which is available to authorized users.

## Background

Smoking is the world’s leading cause of preventable illness and death [1]. One in every two smokers will die of a smoking-related disease, unless they quit [2, 3]. In high-income countries, smoking prevalence has decreased from 46% during the 1970s to about 19% in recent years [4–6]. However, smoking prevalence amongst people with mental disorders has declined only slightly and is currently around 32.0% [7, 8]. In the UK, recent estimates indicate that 33.7% of people with depression, and 28.9% of people with anxiety smoke [7, 8]. They are more heavily addicted, suffer from worse withdrawal [9, 10] and experience a 19% reduction in the odds of quitting (odds ratio 0.81, 95% CI 0.67 to 0.97) [10], even though they are motivated to quit [11]. These inequalities contribute to a reduction in life expectancy of up to 13.6 years for people with depression/anxiety compared to the general population [12, 13].

Traditionally, mental health and addictive behaviours have been treated separately. More recently, there has been a movement towards interventions that target both mental health and addiction [14–16]. Studies in patients with severe mental disorders or alcoholism have shown that treating addiction and mental health in parallel results in meaningful improvements in both [17–21]. van der Meer and colleagues conducted a Cochrane review of smoking cessation treatments for people with current and historical depression [21] and found that adding psychosocial mood management to usual smoking cessation treatment (e.g., nicotine replacement therapy) moderately increased cessation rates when compared to usual smoking treatment alone (risk ratio of 1.47; 95% confidence interval 1.13 to 1.92) [21], thus highlighting the importance of psychological support during a quit attempt for this group.

New evidence suggests that smoking can cause mental illness [45], and that stopping smoking is associated with mental health benefits equal to anti-depressant treatment [22]. In England, people with depression/anxiety have access to psychological therapy services, known as ‘Improving Access to Psychological Therapies’ (IAPT), in which service users receive psychological therapies for depression and anxiety. IAPT may be an ideal platform for delivering smoking cessation treatment. However, there have been no trials comparing the effectiveness of offering smoking cessation treatment alongside usual care, and therefore, it is unknown if such a treatment is feasible and acceptable to service users and therapists, and can be implemented into the service. We have spent the last 9 months designing an intervention with stakeholders to enhance intervention suitability. In this study, we aim to assess: (1) the feasibility of recruiting and retaining participants, collecting data required for a full-sized RCT, and randomisation procedures; (2) the acceptability of data collection procedures and the smoking cessation treatment as delivered alongside usual IAPT care, as perceived by IAPT therapists and study participants; and (3) implementation of the smoking cessation treatment programme.

## Methods

### Design

A randomised and controlled multicentre feasibility trial with nested qualitative research will be conducted to test the acceptability, feasibility and implementation of smoking cessation treatment offered alongside usual psychological care. The study has been registered on the World Health Organization's International Clinical Trials Registry Platform (ID: ISRCTN99531779). Any changes to the methods outlined in this protocol will be outlined in the report of the study findings.

### Ethical review

This study received ethics approval from the National Health Service (NHS) Research Ethics Committee on 19/03/2018 (IRAS ID: 239339). In the case that there are any protocol modifications, these will be submitted for ethical review.

### Setting

This is a multicentre study involving two Improving Access to Psychological Therapies (IAPT) sites in the UK (i.e., Bristol and Oxford). IAPT is a NHS primary-care based psychological therapy service (https://www.england.nhs.uk/mental-health/adults/iapt/). IAPT offers low- and high-intensity evidence-based therapies (e.g., cognitive behavioural therapy (CBT)) to people with common mental disorders. Psychological treatment is delivered by therapists named ‘psychological wellbeing practitioners’ (PWPs) and usually consists of six 30–45-minute sessions, delivered over the telephone or face-to-face (further details below).

### Project timeline

The study will be undertaken over 18 months, and the final follow-up will be in September 2019 (see Additional file 1 for a detailed study timeline and Table 1 and Fig. 1 for a ‘Standard Protocol Items: Recommendations for Interventional Trials (SPIRIT)’ [23] schedule of enrolment, interventions and assessments, and study flow chart).

**Table 1 Tab1:**
[figure not shown]
SPIRIT schedule of enrolment, interventions and assessments

**Fig. 1 Fig1:**
[figure not shown]
Flow chart of study events

### Eligibility criteria

#### Participants (IAPT service users)

The inclusion criteria are as follows:Aged 18 years or olderHas current diagnosis of depression (clinician-administered PHQ-9 score of ≥ 10) and/or anxiety (clinician-administered GAD-7 score of ≥ 8) (note: other mental health comorbidities are allowable)Self-reported, daily tobacco smoker of at least 1 yearInterested in receiving help to quit smoking tobaccoEligible for IAPT treatment on a one-to-one basis over the telephone or face-to-faceAbout to start psychological therapy for depression/anxiety in IAPT

The exclusion criteria are as follows:Already started IAPT treatmentConsidered too unwell by the research or IAPT teamPregnant or breastfeeding

#### Psychological wellbeing practitioners (PWPs, IAPT therapists)

The inclusion criteria are as follows:Aged 18 years or olderHave provided psychological treatment to people with depression/anxiety in IAPT for at least 2 yearsAvailable to attend training in delivering the smoking cessation interventionNon- or ex-smoker

### Withdrawal of participants

Patient and PWP participants can withdraw from the study at any time, and they can withdraw their data from the study at any time during the study period.

### Payments to participants

Participants will not be paid for their contribution to the study.

### Intervention arm

In both the intervention and control groups, participants will receive an evidence-based psychological therapy (i.e., CBT), typically lasting 30–45 minutes per session, delivered over 6 sessions. In the intervention group only, participants will receive a multi-component smoking cessation treatment that includes behavioural, psychological and pharmacological support. PWPs will deliver the smoking cessation treatment as parallel to usual IAPT care (see Table 2). The smoking cessation treatment package is an adapted version of the National Centre for Smoking Cessation and Training’s (NCSCT) standard treatment programme [24]. The NCSCT standard treatment programme is based on the most up-to-date evidence available, is supported by the National Institute for Clinical Excellence and is proven to be cost-effective in NHS settings [25, 26]. The smoking cessation treatment will be delivered over the telephone or face-to-face (i.e., depending on usual care) and will be delivered on an individual basis. Based on interviews and consultation with stakeholders, the intervention has been altered to best fit IAPT usual care, and service user needs, while being mindful of the NCSCT’s standard treatment programme.

**Table 2 Tab2:** Overview of treatment components

Session	1	2	3–5	6
Duration in minutes	10–15	10–15	5–10	5–10
Smoking cessation treatment session	Pre-quit	Quit day	Follow-up	Final
Address participant beliefs about smoking and mental health	✓	✓	✓	✓
Inform the participant about the treatment programme	✓			
Assess current smoking	✓			
Assess past quit attempts	✓			
Explain how smoking dependence develops and assess nicotine dependence	✓			
Explain the importance of abrupt cessation and the ‘not a puff’ rule	✓	✓	✓	✓
Inform the participant about withdrawal symptoms	✓			
Discuss stop smoking medications/products	✓			
Set the quit date	✓			
Prompt a commitment from the participant	✓	✓		
Check on participant progress			✓	✓
Confirm participant readiness and ability to quit		✓		
Confirm that the participant has a sufficient supply of stop smoking medication/products		✓	✓	✓
Give participant NRT vouchers or refer to pharmacy/GP for varenicline	✓	✓	✓	✓
Enquire about medication use			✓	✓
Discuss withdrawal symptoms and cravings, and how to cope		✓	✓	
Advise on changing routine		✓		
CO-monitoring (i.e., site dependent)	✓	✓	✓	✓
Discuss how to address the issue of the participant's smoking contacts and how the participant can get support during their quit attempt		✓		
Discuss any difficult situations experienced and methods of coping			✓	✓
Address any potential high-risk situations in the coming week		✓	✓	
Discuss plans and provide a summary	✓	✓	✓	✓

#### Duration and number of sessions

Participants will receive 5–15 minutes of smoking cessation treatment per IAPT appointment, delivered over 6 IAPT usual care appointments. In Bristol, PWPs will deliver smoking cessation treatment within the usual care timeframe. In Oxford, PWPs will be allocated an extra 5–15 minutes per IAPT appointment to deliver the smoking cessation treatment. We predict that treatment will last approximately 12 weeks; however, this is subject to the progress of the participant's IAPT care. During the first two IAPT appointments, 10–15 minutes will be allocated to delivering the smoking cessation treatment, and the remaining time will be used to deliver IAPT usual care. For the following four IAPT appointments, 5–10 minutes will be used to deliver the smoking cessation treatment, and the remaining time will be used to deliver IAPT usual care.

#### Behavioural and psychological components

PWPs will offer behavioural support as outlined in the NCSCT's standard treatment programme [24]. See Table 2 for an outline of the modified version of the standard treatment programme that will be delivered in this study. In addition to behavioural support, participants will receive psychoeducation about smoking and mental health. New evidence suggests that smoking can cause mental illness [45], and that stopping smoking is associated with mental health benefits equal to anti-depressant treatment [22]. This can partially be explained by breaking the smoking withdrawal cycle—in sum, nicotine has a short half-life, and smokers start to experience the psychological symptoms of withdrawal soon after having a cigarette, for example, symptoms of low mood and anxiety. Therefore, the smoker is in a constant state of withdrawal, with short periods of relief only when they are actively smoking and shortly after finishing a cigarette. It may be that smokers mistake the ability of smoking to relieve withdrawal symptoms to its ability to relieve stress, anxiety and low mood. [27, 28]. Participants will receive an information pack about quitting smoking and mental health via email, leaflet or post.

#### Nicotine replacement therapy (NRT)

NRT will be provided at cost of prescription, or free-of-charge (i.e., depending on site), alongside behavioural support to use NRT (NCSCT and the British National Formulary [24, 29]). NRT will be posted or participants will be given a prescription request to present at their local pharmacy (i.e., depending if IAPT care is delivered over the telephone or face-to-face). In both sites, participants will receive an information pack that includes text and video instructions on how to take the NRT. Participants who self-report having diabetes mellitus, renal impairment or hepatic impairment will be referred to their GP or pharmacy prescriber for NRT [29].

Participants will be provided with two NRT products, and the participant will have the opportunity to alter the dose or type of NRT [24]. As per the NCSCT’s standard treatment programme, participants will be provided with nicotine patches, and the strength will depend on the level of nicotine dependency as assessed using the Heaviness of Smoking Index [30]. A second NRT product will be recommended to help combat cravings—participants will have a choice of a lozenge, gum, microtab, nasal spray, mouth-spray, mini lozenges, or strips, with strength depending on the level of nicotine dependency. See Additional file 1 for the list of NRT products available.

#### Varenicline

If the participant prefers not to use NRT or has previously used NRT as part of a behavioural treatment and failed to quit, they will have the option of using varenicline, pending confirmation from their GP/pharmacy. The participant’s GP or pharmacist prescriber will prescribe varenicline at their discretion. Participants will receive behavioural support for use of varenicline as outlined by the NCSCT [24] and in Table 2.

#### E-cigarettes

PWPs will provide behavioural support to participants who choose to use e-cigarettes to aid their quit attempt. This follows recommendations from Public Health England [31]. However, the study will not fund the purchase of e-cigarettes or accessories.

#### Differences between NCSCT’s standard treatment programme for smoking cessation and the smoking cessation treatment offered in this study

To tailor the smoking cessation treatment to IAPT usual care, we have interviewed PWPs, service managers and service users (NHS National Research Ethics Service review ID:225399. i.e., under write-up) and consulted with current and prospective commissioners for IAPT services. Based on interviews and consultations, we modified the NCSCT’s standard treatment programme as follows:Shortened total treatment time from 110 minutes to 40 to 70 minutes to meet IAPT service requirementsCO-monitoring will not be part of the intervention in one of the sites, as IAPT care is predominately telephone-based in one of the two sitesThere will be an emphasis on addressing the relationships between smoking, the withdrawal cycle and links to mental health

#### Integrating smoking cessation treatment into IAPT usual care

IAPT is predominately based on a guided self-help model. The main aim of guided self-help is to support the service user in learning how to make positive changes to their behaviour and thinking, to help improve their mental health. With support from their PWP, service users learn a toolkit of coping strategies to help them to become their own therapist, so that they can manage their mental health effectively and prevent future setbacks. Pre-trial interviews with PWPs and IAPT service users, and service managers have identified that there are many psychological theories and techniques that PWPs regularly use that provide opportunities to deliver behavioural and psychological support to aid smoking cessation, for example, motivational interviewing, psychoeducation and behavioural activation.

### Control arm

Participants in the control arm will receive IAPT usual care, plus contact details for their local smoking cessation service during their final IAPT appointment.

### PWP training programme

A maximum of ten PWPs per site will be trained to deliver the treatment. PWPs will take part in the following training:NCSCT level 1 online training and assessment programmeNCSCT level 2 face-to-face trainingAn overview about the importance of randomised trial methodology and study procedures (e.g., data recording)A researcher will visit each service once a month to listen in sessions and offer feedback to PWPs

### Outcomes

The trial aims to assess: (1) the feasibility of recruiting and retaining participants, collecting data required for a full-sized RCT, and randomisation procedures, (2) the acceptability of data collection procedures and the smoking cessation treatment as delivered alongside usual IAPT care, as perceived by PWPs and study participants, and (3) implementation of the smoking cessation treatment programme.

#### Main acceptability and feasibility outcome

*Study completers*: Participants will be considered a completer if they continue with smoking cessation treatment up until the point of smoking cessation, a quit attempt, or completion of IAPT care. The proportion of study completers will be calculated by:

$$ \frac{N\ \mathrm{study}\ \mathrm{completers}}{N\ \mathrm{randomised}\ \mathrm{at}\ \mathrm{baseline}} $$

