#### Primary and secondary feasibility measures

We will present the number of participants who were screened, randomised, treated, and followed up for primary outcome in a CONSORT-style flow chart. The proportion of study completers, by trial arm, will be calculated as:$$ \frac{N\ \mathrm{study}\ \mathrm{completers}}{N\ \mathrm{randomised}\ \mathrm{at}\ \mathrm{baseline}} $$

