### Strengths and limitations

In our previous study, we interviewed PWPs, service managers and service users (NHS National Research Ethics Service review ID: 225399, i.e., under write-up), and consulted with current and prospective commissioners for IAPT services in the aim of tailoring the smoking cessation treatment to IAPT usual care. The smoking cessation treatment package used in this study is an adapted version of the National Centre for Smoking Cessation and Training’s (NCSCT) standard treatment programme [24]. The NCSCT standard treatment programme is based on the most up-to-date evidence available and is proven to be cost-effective in NHS settings [25]. We tailored the NCSCT treatment package to best suit the needs of the target population and IAPT service. To optimise the likelihood of successful delievery of the smoking cessation intervention in these settings, we altered the NCSCT standard treatment programme in three ways:We shortened the total treatment time from 110 minutes to 40 to 70 minutes to meet IAPT service requirements. It is possible that shortening treatment time may limit the effectiveness of the intervention. However, a recent Cochrane review found no clear evidence that decreasing the *duration* of personal contact time altered the effect of combined behavioural and pharmacological treatment for smoking cessation [43]. There is an association between *number of contacts* offered for cessation and increased chances of quitting; however, a Cochrane review found that this is not a dose-response relationship and that offering four or more contacts was more effective than offering three or fewer contacts [44]; therefore, participants in our study will be receiving an adequate number of contacts (i.e., six appointments).Carbon monoxide (CO) -monitoring will not be part of the intervention in one of the sites, as IAPT care is telephone-based in one of the two sites. During co-design, we explored whether or not it was possible to use CO-monitors in the behavioural programme; however, feedback from PWPs and service managers was unanimous and indicated that it was not feasible to implement CO-monitoring these settings. We cannot predict whether or not this will alter the effectiveness of the smoking cessation intervention, and our pilot and feasibility study will not be large enough to explore the impact of this on intervention effectiveness. However, if we find that the intervention is feasible, accepted and suitably implemented, this is something that we can adjust for in a definitive RCT.One aspect of this study that is not included in the NCSCT Standard Treatment Programme but will be added to the IAPT smoking cessation treatment will be psychoeducation about smoking and mental health. New evidence suggests that smoking can cause mental illness [45], and that stopping smoking is associated with mental health benefits, potentially equivalent to taking anti-depressants [22]. This evidence can partially be explained by breaking the tobacco withdrawal cycle [27, 28]. In summary, nicotine has a short half-life, and smokers start to experience the psychological symptoms of withdrawal soon after having a cigarette, for example, symptoms of low mood and anxiety. Therefore, the smoker is in a constant state of withdrawal, with short periods of relief only when they are actively smoking and shortly after finishing a cigarette. It may be that smokers mistake the ability of tobacco to relieve withdrawal symptoms to its ability to relieve stress, anxiety and low mood [27, 28]. PWPs will integrate this evidence into treatment sessions.

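### The main outcome is labelled retention in treatment but stops counting at the first quit attempt, scheduled for session 2 of 6, and it has no meaning in the control arm

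*Protocol article*

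**What the plan says.** Four parts of the protocol article bear on this.

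- **Label.** The abstract states: "The main outcome will be retention in the smoking cessation treatment". The Sample size section likewise plans for a 40% rate of continuing with that treatment in the intervention arm.
- **Definition.** Under Main acceptability and feasibility outcome, a completer is someone who will "continue with smoking cessation treatment up until the point of smoking cessation, a quit attempt, or completion of IAPT care". The three end points are joined by 'or', and the count is divided by the number randomised at baseline.
- **Schedule.** In Table 2 (Intervention arm) the row "Smoking cessation treatment session" runs from pre-quit (session 1) and quit day (session 2) through follow-up (sessions 3–5) to final (session 6). The section on duration adds: "Participants will receive 5–15 minutes of smoking cessation treatment per IAPT appointment, delivered over 6 IAPT usual care appointments".
- **Arms.** Primary and secondary feasibility measures says: "The proportion of study completers, by trial arm, will be calculated as", followed by the same formula. The Control arm section says: "Participants in the control arm will receive IAPT usual care, plus contact details for their local smoking cessation service during their final IAPT appointment". The Intervention arm section gives smoking cessation treatment to the intervention group only.

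**The concern.** A figure reported as retention will be read as the share of people who stayed with the programme. Here the clock stops at the first quit attempt, which the plan schedules for the second appointment. The four later sessions hold the post-quit support, and whether people stay for them inside IAPT care is a large part of what a feasibility study of this package should show. Two services could have the same completer proportion while one keeps most participants to session 6 and the other loses them just after quit day.

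The second difficulty is the control arm. Controls have no smoking cessation treatment to continue with, so the definition cannot be applied to them. Yet the analysis section asks for the proportion in each arm. Whatever is printed in the control column will be either empty or some other quantity under the same name, which invites a between-arm comparison that means nothing.

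**Working it through.** **1. The plan's own figures.** The Sample size section takes 100 participants at follow-up. At 1:1 allocation that is 50 per arm. The exact (Clopper-Pearson) 95% interval for 20/50 is 26.4% to 54.8%, matching the stated 26% to 55%. For 40/100 it would be 30.3% to 50.3%, so the calculation was made for one arm. For the baseline number, 100 / (1 − 0.36) = 156.25, rounded up to 157, which also matches. The sample-size arithmetic is not at fault, and it confirms that the outcome was meant for the intervention arm.

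**2. The least treatment a completer can have had on schedule.** Durations are from Table 2.

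- Sessions 1–2: 2 × (10 to 15) = 20 to 30 minutes
- Sessions 3–6: 4 × (5 to 10) = 20 to 40 minutes
- All six: 40 to 70 minutes, which agrees with the total given elsewhere in the article

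A participant who attempts to quit at session 2 and then leaves has had 2 of 6 sessions and 20–30 of 40–70 minutes, and is a completer.

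**3. How the measure relates to retention through the programme.** Among those randomised to the intervention, let

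- E = the proportion who stay in smoking cessation treatment to the end of IAPT care;
- A = the proportion who stop smoking or attempt to while in treatment, and then leave treatment before the end of IAPT care.

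The definition gives completers = E + A. Since A cannot be negative, the completer proportion is never below E and exceeds it by exactly A. Someone who leaves before any attempt is correctly a non-completer, so early drop-out is captured. Drop-out after an attempt is not.

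**4. How large A might be.** The documents give no figure. As an illustration only, assume that everyone attends session 1, that a constant fraction s continues from each session to the next, that no attempt precedes session 2, and that session 6 is the end of care. The completer proportion then lies between the share reaching session 6 (s to the power 5) and the share reaching session 2 (s).

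| s | Reach session 2 | Reach session 6 |
|---|---|---|
| 0.70 | 70% | 17% |
| 0.80 | 80% | 33% |
| 0.90 | 90% | 59% |

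If 40% reached session 6, s would be 0.40 to the power 1/5 = 0.83, so about 83% would reach quit day. These are outer limits under an assumption of mine, not estimates of bias.

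**5. The control arm.** The definition requires continuing with smoking cessation treatment. Controls receive usual care and, at their last appointment, contact details for a local service. No separate completer definition is given for them. Reading it as completion of IAPT care would make it a different quantity from the intervention-arm figure.

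**6. Precision with the randomised denominator.** With about 78 randomised to the intervention (157 / 2 = 78.5), a rate near 40% is 31/78 = 39.7%, with exact 95% interval 28.8% to 51.5%. Restricting the outcome to that arm needs no more participants.

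**The case against.** The best defence is that the definition is stated openly and reflects a view: a person who has tried to quit has got what the treatment is for, so leaving afterwards is not failure. The measure does capture retention up to the first attempt, and the person must still be in treatment when the attempt occurs. To say that it does not measure retention at all would go too far. This argument supports reporting quit attempts as an outcome. It does not support reporting them as retention when four sessions of post-quit support are still to come.

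It can also be said that other planned data would reveal later drop-out: missed and completed IAPT appointments, drop-out from IAPT, retention recorded by therapists, and the flow chart. That is largely right for people who leave the service. IAPT appointment counts would not by themselves identify someone who stays in IAPT but stops the smoking component, and the main outcome would still carry the wrong label.

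A reader might infer three stronger things that the article does not support.

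- *That the proportion would be taken over all 157 randomised.* The formula in the outcome section names no arm, but the analysis section splits it by arm and the sample size refers to the intervention arm, so a pooled denominator is an unlikely reading.
- *That a two-session completer falls short of an attendance standard set by the protocol.* The Discussion cites evidence that "offering four or more contacts was more effective than offering three or fewer contacts". That concerns contacts offered, and this trial offers six. No minimum attendance is set.
- *That this one number decides feasibility.* The article also lists recruitment, satisfaction, interviews, implementation and data completeness, and ties no go/no-go rule to the completer proportion.

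**Conclusion.** The concern holds in this form: the main outcome measures retention up to the first quit attempt, or to the end of IAPT care where no attempt is made, while its label promises retention in the treatment. It cannot show drop-out after an attempt from sessions 3–6. That conclusion rests on the definition's wording and on the Table 2 schedule, under which the attempt falls at session 2; a participant who attempts later will have had more sessions before becoming a completer. The direction is certain, since the figure cannot be lower than retention to the end of care. The size of the excess cannot be derived from the documents, and no number of percentage points should be attached to it.

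The control-arm proportion has no meaning as defined. This does not bias the intervention-arm figure, but the analysis section asks for something that cannot be computed. Both matter because this is the only outcome designated as main and the one on which the sample size was based.

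**What to change.** - In the outcome section and the analysis section, restrict the proportion to participants randomised to the intervention arm, with the number randomised to that arm as denominator.
- Report retention through the programme from recorded attendance: the distribution of smoking cessation sessions attended (0–6) and the proportion continuing in smoking cessation treatment to the end of IAPT care.
- Report having made a quit attempt, and being abstinent, as separate counts and not as routes to completer status.
- For controls, report completion of IAPT care under that name, and drop the by-arm calculation for this outcome.
- Make the abstract, the outcome definition and the sample-size text describe the same quantity.

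The cost is mainly rewording. Table 3 already has therapists recording retention in the smoking cessation intervention, and planned, completed and missed appointments are collected. If the retention record is not kept by session, one yes/no entry per appointment for whether the smoking component was delivered would be enough. The drawback is that the headline retention figure is likely to be lower. The 40% planning rate should then be described as applying to whichever definition is kept.
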